### Trial design

The trial will take place in a 52-week timeframe, including 26 weeks of treatment in both randomization groups. Metformin will be started at 500 mg b.i.d. (oral) and escalated to 1000 mg b.i.d. (4 tablets of 500 mg (=2000 mg)) 2 weeks thereafter. For participants aged 16–18 years, metformin dosage will be escalated to 500 mg b.i.d*. *maximum. Participants will undergo 4 main face-to-face visits after 0, 13, 26 and 52 weeks, as well as one short telephone visit after 2 weeks to evaluate the study medication dose (Table 1). Meanwhile, participants will undergo a lifestyle intervention that is considered care as usual in the participating centers. The study medication will start in the same seven days as the lifestyle intervention. The lifestyle intervention will exist of a combination of an exercise program and dietary interventions. The dietary intervention consists of five consultations with a dietitian in the first 26 weeks of treatment to stimulate both healthy food and appropriate caloric intake. The exercise program exists of minimally 60 min per week of unsupervised exercise by choice (i.e. walking, dancing, cycling or jogging). Also, participants gather in weekly lifestyle group sessions coached by an exercise professional with affinity in mental healthcare for low-intensity exercise including weekly weight measurements and assessment of physical activity using the Physical Activity Vital Sign questionnaire (PAVS) [40, 41]. Due to the COVID-19 pandemic, the weekly lifestyle sessions will be offered online. Participants may wish to discontinue lifestyle interventions at any moment and still continue with the current trial. Considering that some participants will discontinue lifestyle interventions in clinical practice, participants may carry on with the trial following the pragmatic design of this study to obtain results resembling clinical practice. Similarly, patients may continue with the trial after switching or stopping antipsychotic use. Patients should be on an antipsychotic at the start and may use any additional medicines except for medication(s) that inhibit(s) metabolism of metformin (e.g. bictegravir, cobicistat, daclatasvir, dolutegravir and vandetanib) or otherwise interact(s) with metformin (in particular those with possible detrimental effects on kidney functioning, e.g. NSAIDs, ACE-inhibitors, diuretics and intravascular iodine). Therefore, participants using the aforementioned medication will be excluded from this trial. Changes in medication use will be registered at each visit. Information regarding adherence to medication, dietary and exercise interventions is obtained by self-report during visits after 13 and 26 weeks. In addition, pill counts are used to assess medication use adherence. Participants are considered compliant in case of a pill count of > 80% [42, 43]. The adherence ratio will be calculated by the difference in the number of pills provided at visit 1 and the remaining pills at visit 3 and again between the number of pills provided at visit 3 and the remaining pills at visit 4 divided by the prescribed number of pills. This result will be multiplied by 100. To improve participant retention, participants will receive financial reimbursement for travel costs and 10 euros for each visit. Furthermore, the research team actively involved two experienced experts and patient association Anoiksis in the conceptualization and design of this study to ensure the design is patient-friendly, reflective of clinical practice and beneficial to patients.

**Table 1 Tab1:**
[figure not shown]
Study Flow Diagram

^a^Mini-International Neuropsychiatric Interview

^b^The short version of the official WHO quality of life questionnaire

^c^the 3-level EuroQol scale to describe and value health

^d^Clinical Global Impression

^e^iMTA Productivity Cost-effectiveness questionnaire

^f^iMTA Medical Consumption questionnaire

^g^Brief Psychiatric Rating Scale

^h^Community Assessment of Psychic Experiences

^i^Simple Physical Activity questionnaire

^j^6 Minutes Timed Walking Test

^k^Including height (first visit only), weight, BMI, systolic and diastolic blood pressure, pulse, waist circumference

^l^Including CRP, GFR, LDL, HDL, triglycerides, insulin, glucose, HbA1c

^m^x^a^ – x^b^ Metformin dose 1000 mg daily, x^b^ – x^c^ Metformin dose up to 2000 mg daily

### Assessments

#### Visit 1

During visit 1, baseline demographic characteristics will be assessed. Medical history including medication-, alcohol, tobacco- and substance use, weight before the start of mental illness, weight before the initiation of antipsychotic use and the estimated amount of weight gained due to antipsychotic use is also collected. The M.I.N.I. plus section M is used to assess the criteria for schizophrenia [44, 45]. All elements of MetS (i.e. body weight and height, BMI, waist circumference, and systolic and diastolic blood pressure) are measured during a short physical examination. The 6 Minutes Timed Walking Test (6MTWT) and Simple Physical Activity questionnaire (SIMPAQ) are used to assess physical endurance and physical activity, respectively [46]. Blood glucose levels are measured using a capillary blood fingerdipstick and urine pregnancy tests will be conducted for women of childbearing age. Additionally, blood will be drawn to measure C-reactive protein (CRP), GFR, Triglycerides, Low-density lipoprotein (LDL) and High-density lipoprotein (HDL) levels, insulin, glucose and Hemoglobin A1c (HbA1c). At last, several questionnaires will be assessed during visit 1 (see ‘secondary outcomes’ below).

#### Visit 2

Visit 2 is a short visit by telephone at 2 weeks into the study to assess how the participant is proceeding with the study medication, i.e. whether they have been able to switch from the starting dose of 500 mg b.i.d. to 1000 mg b.i.d. and whether they are experiencing any side effects.

#### Visits 3 and 4

During visits 3 and 4, adherence to lifestyle interventions is assessed, as well as information regarding medication use, dose and side effects, adverse events reactions, alcohol-, tobacco- and substance use. Similarly to visit 1, physical endurance, physical activity and elements of MetS are measured during physical examination additional to the blood glucose level using a capillary blood fingerdipstick. Also, a urine pregnancy test and laboratory tests will be conducted. One EDTA tube (6 cc) or saliva is optionally drawn for DNA extraction. Furthermore, the same questionnaires as during visit 1 will be taken.

#### Visit 5

One year after completing study visit 1, body weight, waist circumference and blood.

pressure are measured during physical examination and the 6MTWT is performed to assess physical endurance [46]. Furthermore, information regarding medication use and the (off-label) prescription of metformin between 26 weeks and 52 weeks by other physicians is assessed.

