### Statistical analysis

#### Sample size calculation

A regression of weight on treatment with a sample size of 128 observations achieves 80% power at a two-sided 0.05 significance level to detect a difference in a weight reduction of two kgs (SD = 4, ES = 0.5) after 26 weeks (PASS 2008, version 8.0.16). We estimate the drop-out rate to be a maximum of 50% as such attrition rates are most commonly reported in trials targeting schizophrenia patients [37]. Drop-outs are those not attending the visit at 26 weeks. As soon as 128 subjects have completed this visit, inclusion will be stopped. Considering the estimated drop-out rate, we will therefore include approximately 256 subjects to ensure that 128 subjects complete the visit at 26 weeks. This power calculation is based on an independent two-sample t-tests of the outcome at 26 weeks. Using linear models in the data analysis will increase the efficiency of the analysis and therefore the power to detect a treatment effect.

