Similar analyses to the abovementioned primary study parameter analyses will be applied to the secondary outcomes, using generalized linear mixed models with appropriate link functions where necessary. For exploratory purposes, the following subgroup analyses within subtypes of patients will be conducted using the same model to explore possible differences in treatment effects: those on clozapine vs. those on other antipsychotics and those on high-risk agents (olanzapine, clozapine and quetiapine, risperidone and paliperidone) vs. all other antipsychotics [2, 12]. In post-hoc sensitivity analysis, the quantitative measure of the amount of self-reported AiWG will be used to examine differences between AiWG and weight gain due to other reasons.

For genetic analyses, we will run a linear model of polygenic risk scores (PRS) for BMI and MetS to assess their association with weight reduction. Covariates will be age, sex and three principal components of genetic ancestry. At each *p*-value threshold going from 5 × 10–8 to, 5 × 10–7, 5 × 10–6, 5 × 10–5, 5 × 10–4, 5 × 10–3, 0.01, 0.05, 0.1, 0.2, 0.3, and 0.4 both the variance in BMI/MetS and the p-value of the association will be computed to visualize the strength of association and degree of explained variance per p-value bin [55]. The optimal p-value threshold will be computed using PRSice (https://www.prsice.info/) or similar methods and reported. The significance threshold is set at *p* < 0.05.

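### The visit text first requests optional DNA at weeks 13 and 26, so uptake may depend on weight response and those who leave before week 13 cannot be genotyped; sampling at visit 1 is a cheap, minor improvement

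*Protocol article*

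**What the plan says.** In the protocol article, Assessments, the visit 1 text describes a blood draw: "Additionally, blood will be drawn to measure C-reactive protein (CRP), GFR, Triglycerides, Low-density lipoprotein (LDL) and High-density lipoprotein (HDL) levels, insulin, glucose and Hemoglobin A1c". It names no DNA sample. The only mention of DNA collection is in the text on visits 3 and 4: "One EDTA tube (6 cc) or saliva is optionally drawn for DNA extraction". Table 1, the visit schedule, is not shown.

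Trial design gives the timing: "Participants will undergo 4 main face-to-face visits after 0, 13, 26 and 52 weeks". Visits 3 and 4 are therefore at weeks 13 and 26. The weekly lifestyle sessions in between involve "low-intensity exercise including weekly weight measurements and assessment of physical activity".

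The genetic analysis is described under Data analysis: "we will run a linear model of polygenic risk scores (PRS) for BMI and MetS to assess their association with weight reduction". At each p-value threshold, "both the variance in BMI/MetS and the p-value of the association will be computed".

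On attrition, Sample size calculation states: "We estimate the drop-out rate to be a maximum of 50" per cent. It defines drop-out as non-attendance at week 26.

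**The concern.** Genotype does not change, and blood is already drawn at visit 1, so the text gives no evident reason to wait. Waiting has two consequences.

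- **Consent comes after the outcome can be known.** By visit 3 the participant has had some three months of study tablets and weekly weighing. The genetic model studies weight reduction. If willingness to give DNA depends on how much weight was lost, the sample is selected on the outcome and the score-to-weight association is distorted.
- **Early leavers are never asked.** A participant who leaves before visit 3 gives no DNA. It then cannot be checked whether leavers and completers differ in their scores, and early leavers cannot enter any weighted or imputed genetic analysis.

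At stake is the aim of assessing whether genetic liability to BMI and MetS helps to estimate weight reduction. The randomised comparison of metformin with placebo is not touched.

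**Working it through.** **Inputs from the protocol article.** 128 observations, 80% power, two-sided 0.05, difference 2 kg, SD 4; drop-out at most 50%; about 256 recruited; inclusion stops once 128 have completed week 26 (all Sample size calculation). Allocation 1:1 (Randomization and blinding).

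**1. The plan's own figures.** Effect size 2/4 = 0.5. The exact two-sample t-test power is 0.795 with 63 per arm and 0.801 with 64 per arm, so 2 × 64 = 128. Inflation: 128/(1 − 0.5) = 256. Both figures reproduce.

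**2. How many could be asked for DNA.** At visit 1: about 256. At visit 4: about 128 under 50% drop-out. Visit 3 attendance is not given, so the number who could be asked at visits 3 and 4 together lies between 128 and 256, before refusals.

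**3. Effect on the analysis of weight reduction.** Anyone with a week-26 study weight attended visit 4 and could be asked for DNA there. The set with both DNA and a week-26 weight is therefore capped near 128, whether DNA is taken at visit 1, 3 or 4. Timing costs this complete-case analysis no participants.

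**4. Effect of response-dependent uptake.** This was simulated with 2 million participants: weight loss = b × score + 2 kg × arm + error, within-arm SD 4 kg, and b = 4 × sqrt(R²). This gives b = 0.566 for R² = 2% and 0.894 for R² = 5%. Retention was a random 50%. Uptake was 70% at average weight loss, with its odds multiplied by the stated ratio per SD of weight loss. The table gives the estimated slope divided by the true slope, adjusted for arm.

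| Odds ratio per SD | R² = 2% | R² = 5% |
|---|---|---|
| 1 (no dependence) | 0.994 | 0.997 |
| 1.5 | 0.957 | 0.977 |
| 2 | 0.909 | 0.921 |
| 3 | 0.859 | 0.843 |

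The first row is 1 apart from simulation noise. The other rows give attenuation from 1 − 0.977 = 2% to 1 − 0.843 = 16%. The R² values, the 70% and the odds ratios are assumptions; the document gives none of them.

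**5. If the variance in BMI/MetS means baseline traits.** Only DNA and visit 1 values are then needed, and the ratio of standard errors is sqrt(256/n), with n the number who could be asked at visits 3 and 4:

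- n = 256: 1.00
- n = 192 (half of the 128 drop-outs attend visit 3, an assumption): sqrt(256/192) = 1.15
- n = 128 (no drop-out attends visit 3): sqrt(256/128) = 1.41

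The correlation detectable with 80% power at two-sided 0.05 is tanh[(1.960 + 0.842)/sqrt(N − 3)]: 0.174 for N = 256 (R² 3.0%), 0.201 for N = 192 (4.0%) and 0.245 for N = 128 (6.0%).

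**The case against.** The strongest objection is that drop-out, not DNA timing, causes most of the selection. A reader might infer that late sampling shrinks the genetic analysis of weight reduction or makes it a retained-only analysis. The document does not support that: by step 3, a participant without a visit 3 or visit 4 weight has no study-visit outcome from the treatment period, wherever DNA is taken. This part of the objection stands in full.

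It also stands that response-dependent consent is a risk and not a stated fact. A reader might take the sample to be selected on the response already seen, but nothing in the document says that uptake follows response. Without such dependence there is no bias.

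The 1.41 is an upper bound for a baseline association. The Data analysis text does not clearly plan one; its phrase about variance follows directly on the aim concerning weight reduction. The bound also needs drop-out at its stated maximum and no drop-out attending visit 3.

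One might further infer that participants with online visits can never give DNA. That is not supported either: COVID-19 measures also allows house visits, and saliva is accepted in place of blood.

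Finally, Table 1 is not shown and could list DNA at visit 1. If it does, the visit text should be brought into line with it.

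What the objection does not remove is that the text seeks consent after allocation and after weight change can be known, and that DNA not collected from early leavers cannot be obtained later by analysis.

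**Conclusion.** The point holds as a minor design improvement confined to the polygenic-score aim. On the visit text, optional DNA is first requested at week 13, so uptake may depend on response and those who leave before visit 3 cannot be characterised genetically.

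The possible harm ranges from no bias to a slope attenuated by about 2 to 16%, the latter only under assumed odds ratios of 1.5 to 3 per SD of weight loss. There is no loss of size in a complete-case analysis of week-26 change. For baseline associations, if these are intended, the standard error is inflated by a factor between 1 and 1.41, depending on visit 3 attendance. The primary comparison and its power are unaffected. The conclusion rests on the narrative visit text, with Table 1 unseen.

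**What to change.** Offer the optional EDTA tube or saliva sample at visit 1 with the existing blood draw. Under Randomization and blinding, the code is released only after all baseline assessments, so consent would then precede both allocation and response. Keep visits 3 and 4 as a fallback for anyone not sampled. Compare polygenic scores between dropouts and completers, and say whether the variance in BMI/MetS refers to baseline values; if so, estimate it in all genotyped randomised participants.

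The cost is one optional tube or saliva sample moved to an existing visit, plus storing and genotyping some extra samples from participants who later drop out. The change does not enlarge the complete-case week-26 analysis. Its gain is consent free of response and the ability to describe early leavers genetically.

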### Primary outcome

Difference in body weight as a continuous trait between the two arms from treatment inception until 26 weeks of treatment.

### Secondary outcomes

Differences between the two arms from treatment inception until 26 weeks of treatment in:
Any element of MetS (i.e., waist circumference (cm), BMI (kg/m^2^), triglycerides (mmol/L), LDL (mmol/L) and HDL (mmol/L) levels in blood, blood pressure (mmHg) and HbA1c (mmol/mol)) [3].Response, defined as ≥5% body weight loss at 26 weeks relative to treatment inception.Quality of life measured using the WHOQOL-BREF, a shorter version of the World Health Organization Quality of Life instrument [47].Quality of life measured using the complementary 3-level version of the EuroQol 5D (EQ-5D-3L) [48].General psychological and physical health using the brief Clinical Global Impression-Severity and -Improvent scale (CGI-S and CGI-I) [49].General psychological and physical health using the Brief Psychiatric Rating Scale (BPRS) [50].Potential fluctuations in depressive, positive and negative symptoms using the The Community Assessment of Psychic Experiences (CAPE) scale [51, 52].Cost-effectiveness using the iMTA Productivity Cost Questionnaire (iPCQ) and the iMTA Medical Consumption Questionnaire (iMCQ) [53].

### COVID-19 measures

During the face-to-face visits, measures will be taken in accordance with applicable guidelines regarding COVID-19 if necessary to optimize safety. Face-to-face visits can be adjusted as much as possible to online visits or house visits if required. The weekly lifestyle sessions will be offered online. Furthermore, the research team will use adequate protective equipment and will keep a physical distance of 1.5 m wherever possible. Additionally, participants will be asked to:
keep a physical distance of 1.5 m from othersavoid handshakingcough and sneeze in the elbowpractice good hygiene (disinfect, wash hands)stay home if any cold or flu symptoms are presentcome to the face-to-face visits alone if possible

As in practice it may not be feasible for participants to attend the next visit exactly after 13 and 26 weeks, respectively, we allow for a 4-week time window for these visits, i.e. a participant should attend to the next visit within 11–15 weeks and 24–28 weeks, respectively. This is in line with clinical practice and the pragmatic nature of this trial: participants suffering from psychosis often miss follow-up consultations (due to hospitalization, negative symptoms or symptom exacerbation) and are then scheduled some weeks later. Furthermore, participants may be unable to attend due to COVID-19 symptoms. Participants with suspected or diagnosed COVID-19 may continue the trial whenever they are fully recovered within this time window.

### Data collection

Local authorized investigators will enter the acquired data and examination results into hard-copy documents and an electronic case record form (eCRF), Castor, that is accessible via the internet [54]**.** Investigators will receive personal user names and passwords for this purpose, and data will be encrypted for transfer. The investigator must (electronically) sign that entries into the eCRF are true and complete. After data has been submitted to the study centre, another thorough inspection of the completeness and plausibility of entries will be conducted. If needed, clarification questions will be addressed to the sites. Only after all questions regarding data quality have been answered, the database will be locked.

Pseudonymous (coded) data will be relayed to the central study team for scientific analysis or made available, if necessary, to the responsible supervisory authority. Only qualified and authorised collaborators of the study sponsor will enter the pseudonymous data into a computerised database. The acquired data will be used without participants’ names for scientific analysis and participants’ names will not be mentioned in any publication.

### Statistical analysis

#### Sample size calculation

A regression of weight on treatment with a sample size of 128 observations achieves 80% power at a two-sided 0.05 significance level to detect a difference in a weight reduction of two kgs (SD = 4, ES = 0.5) after 26 weeks (PASS 2008, version 8.0.16). We estimate the drop-out rate to be a maximum of 50% as such attrition rates are most commonly reported in trials targeting schizophrenia patients [37]. Drop-outs are those not attending the visit at 26 weeks. As soon as 128 subjects have completed this visit, inclusion will be stopped. Considering the estimated drop-out rate, we will therefore include approximately 256 subjects to ensure that 128 subjects complete the visit at 26 weeks. This power calculation is based on an independent two-sample t-tests of the outcome at 26 weeks. Using linear models in the data analysis will increase the efficiency of the analysis and therefore the power to detect a treatment effect.

#### Data analysis

The primary analysis in this trial tests the effect of metformin use next to care as usual including lifestyle interventions on body weight with a primary comparison at 26 weeks after treatment onset. This will be analyzed using a general linear mixed model with treatment group, baseline weight, gender, age, timepoint (as categorical factor) and compliance with lifestyle therapy as fixed factors and patient as random factors. Measurements of visit 3 (week 13) and visit 4 (week 26) will be included in the primary analysis models. Missing baseline parameters will be imputed before the analyses, but mixed models can handle missing outcome variables at post-randomization weeks if these are missing at random (MAR). The pattern of missingness will be examined. As a sensitivity analysis, body weight at 26 weeks will also be analyzed using an ANCOVA with treatment group and gender as factors and baseline weight and age as covariates. The significance threshold is set at *p* < 0.05. Considering the study population, we expect a high number of dropouts [37]. Additionally, we expect participants within one stratification group may switch clozapine or other antipsychotic use. Taking into account the pragmatic design of this study, the Intention-To-Treat principle will be followed for the primary and secondary analyses. In secondary analysis, the effect of metformin on body weight after 26 weeks of treatment will be compared to body weight at 52 weeks after 26 weeks of non-treatment with metformin. In this way, we can examine whether the possible effect of metformin on AiWG continues after 26 weeks of non-treatment following discontinuation of metformin use after 26 weeks of treatment. In a sensitivity analysis, per-protocol analysis will be applied for all analyses. Non-adherent participants to study medication defined as less than 80% of pills being taken will be excluded (see ‘Trial design’) [42, 43].

Similar analyses to the abovementioned primary study parameter analyses will be applied to the secondary outcomes, using generalized linear mixed models with appropriate link functions where necessary. For exploratory purposes, the following subgroup analyses within subtypes of patients will be conducted using the same model to explore possible differences in treatment effects: those on clozapine vs. those on other antipsychotics and those on high-risk agents (olanzapine, clozapine and quetiapine, risperidone and paliperidone) vs. all other antipsychotics [2, 12]. In post-hoc sensitivity analysis, the quantitative measure of the amount of self-reported AiWG will be used to examine differences between AiWG and weight gain due to other reasons.

For genetic analyses, we will run a linear model of polygenic risk scores (PRS) for BMI and MetS to assess their association with weight reduction. Covariates will be age, sex and three principal components of genetic ancestry. At each *p*-value threshold going from 5 × 10–8 to, 5 × 10–7, 5 × 10–6, 5 × 10–5, 5 × 10–4, 5 × 10–3, 0.01, 0.05, 0.1, 0.2, 0.3, and 0.4 both the variance in BMI/MetS and the p-value of the association will be computed to visualize the strength of association and degree of explained variance per p-value bin [55]. The optimal p-value threshold will be computed using PRSice (https://www.prsice.info/) or similar methods and reported. The significance threshold is set at *p* < 0.05.

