## Discussion

Here, we describe the design of a pragmatic, randomized, double blind, multicenter controlled clinical trial to investigate whether metformin up to 2000 mg daily for 26 weeks in combination with treatment as usual including lifestyle interventions reduces AiWG in comparison to placebo in combination with lifestyle interventions.

The current trial has the following added value over earlier published trials regarding [29]. First, in line with clinical practice, where many patients treated with a range of antipsychotics report AiWG, inclusion is not restricted to certain antipsychotics, thus allowing us to evaluate whether this combination treatment is effective in the entire group of antipsychotics users. Second, the inclusion criteria are less strict than in previous trials, thus ensuring that the study population reflects clinical practice where some patients are not given a diagnosis of schizophrenia (but of another psychotic disorder) and may experience weight gain as problematic even if this is less than 10% (weight gain > 10% was an inclusion criterion in the Chinese 2008 trial) [28]. Third, the intervention is more feasible. The exercise program for participants in the current trial is less intense than other exercise programs: for example, our exercise program consists of two sessions weekly as opposed to seven in the published trial [28]. We expect that this increases feasibility and thus the likelihood of implementation in this patient group. Fourth, this is the first clinical trial examining the use of metformin in addition to lifestyle therapy for the treatment of AiWG in residents of a North-Western European country. This is relevant as cultural and genetic vulnerability factors may influence treatment adherence and efficacy. Fifth, we treat patients for 26 weeks as opposed to 12 weeks in the published trial, thus allowing us to better ascertain drop-outs and temporal patterns in treatment response [28]. At last, as it is currently impossible to predict who will benefit from treatment of AiWG with metformin we also include genetic analyses to assess whether polygenic risk scores are associated with metformin treatment response.

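### The listed primary mixed model pools weeks 13 and 26 without a treatment-by-timepoint term, so its treatment coefficient is not the week-26 difference that the plan names and is sized on

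*Protocol article*

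**What the plan says.** All references are to the protocol article.

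- **Primary outcome** defines the endpoint as "Difference in body weight as a continuous trait between the two arms from treatment inception until 26 weeks of treatment".
- **Data analysis** says that the primary analysis tests the effect of metformin "on body weight with a primary comparison at 26 weeks after treatment onset". The model for this is a "general linear mixed model with treatment group, baseline weight, gender, age, timepoint (as categorical factor) and compliance with lifestyle therapy as fixed factors". Patient is the only random factor.
- The same section adds: "Measurements of visit 3 (week 13) and visit 4 (week 26) will be included in the primary analysis models".
- It also plans an ANCOVA of week-26 weight, labelled a sensitivity analysis.
- **Sample size calculation** uses a 2 kg difference with SD 4 after 26 weeks and states: "This power calculation is based on an independent two-sample t-tests of the outcome at 26 weeks". Dropout is put at no more than 50% and means missing the week-26 visit.

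Neither a treatment-by-timepoint interaction nor a model-based week-26 contrast appears anywhere in the article.

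**The concern.** With treatment and timepoint entered additively and two post-baseline visits in the outcome, the model assumes one treatment effect common to both visits. No week-26 difference distinct from week 13 can be taken from it. The named comparison and the basis of the sample size are week-26 quantities, but the confirmatory p-value would test a blend of the two visits.

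The error can run either way. If the effect grows between visits, the coefficient understates the week-26 difference. If an early effect fades, the coefficient overstates it, and a transient benefit could be reported as a week-26 result. The Objectives section says that a significant result would allow guidelines to include metformin, so it matters which quantity is tested. Data analysis also carries similar models over to the secondary outcomes.

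**Working it through.** **Inputs from the article:** 128 completers, so n = 64 per arm under 1:1 allocation; difference 2 kg; SD σ = 4; two-sided 0.05; 256 recruited, so 128 per arm, of whom at most 128 − 64 = 64 could have week 13 only.

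**Assumed, because the article does not give them:** the week-13 effect δ13; the week-13 SD (4, with 3 as an alternative); the residual correlation ρ between visits, 0.5 to 0.85; and m, the number per arm with week 13 only (0, 32 or 64). SD 4 is treated as the residual SD, and the other covariates are ignored.

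**1. The plan's own figure.** A two-sample t-test with 64 per arm and effect size 2/4 = 0.5 has power 0.801 (0.795 with 63 per arm). 128/(1 − 0.5) = 256. Both figures reproduce.

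**2. What the listed model estimates.** For a random-intercept model with categorical time and equal arms, generalised least squares gives

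coefficient = w·δ26 + (1 − w)·δ13, with w = n / [2n + m(1 + ρ)].

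- m = 0: w = 64/128 = 0.50
- m = 32: w = 64/(128 + 48) = 0.364 at ρ = 0.5; 64/(128 + 59.2) = 0.342 at ρ = 0.85
- m = 64: w = 64/(128 + 96) = 0.286 at ρ = 0.5; 64/(128 + 118.4) = 0.260 at ρ = 0.85

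**3. Week-26 effect 2 kg, week-13 effect 1 kg.** The coefficient is 1 + w. With SD 4 at both visits, SE² = 2σ² / [2n/(1 + ρ) + m] and power = Φ(coefficient/SE − 1.96). For example, at m = 0 and ρ = 0.85, SE² = 32/(128/1.85) = 0.4625, SE = 0.680 and power = Φ(1.50/0.680 − 1.96) = 0.60. With SD 3 at week 13, the weights are as above and the SE uses the actual variances. For example, at m = 0 and ρ = 0.85, SE² = (2/64)(9 + 16 + 2 × 0.85 × 12)/4 = 0.355, SE = 0.596 and power = 0.71.

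| m per arm | Coefficient (kg) | Power, SD 4 and 4 | Power, SD 3 and 4 |
|---|---|---|---|
| 0 | 1.50 | 0.60–0.69 | 0.71–0.80 |
| 32 | 1.34–1.36 | 0.67–0.74 | 0.81–0.87 |
| 64 | 1.26–1.29 | 0.73–0.79 | 0.88–0.92 |

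**4. Other week-13 effects** (week-26 effect 2 kg, SD 4 at both visits, over the same m and ρ):

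| Week-13 effect (kg) | Coefficient (kg) | Power |
|---|---|---|
| 0.5 | 0.89–1.25 | 0.44–0.53 |
| 1.5 | 1.63–1.75 | 0.73–0.94 |
| 2.0 | 2.00 | 0.84–0.99 |

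**5. No week-26 effect, week-13 effect 1 kg** (SD 4, ρ = 0.7).

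- m = 0: coefficient 0.50, SE = √(32 × 1.7/128) = 0.652. Rejection in favour of metformin is Φ(0.50/0.652 − 1.96) = 0.12.
- m = 64: w = 64/(128 + 108.8) = 0.270, coefficient 0.73, SE = √[32/(75.3 + 64)] = 0.479. Rejection is Φ(0.73/0.479 − 1.96) = 0.33.

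The nominal rate in that direction is 0.025.

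**6. With treatment-by-timepoint added.** The week-26 contrast is 2.00 kg in every scenario of steps 3 and 4. With SD 4, SE² = 2σ²[(1 − ρ²)/n + ρ²/(n + m)].

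- m = 0: SE² = 32/64 = 0.5, SE = 0.707, power 0.807 by the normal approximation, matching the design.
- m = 32, ρ = 0.5: SE = 0.677, power 0.84.
- m = 64, ρ = 0.85: SE = 0.565, power 0.94.

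**The case against.** The best defence is that the article lists variables and not a full model formula. It names the week-26 comparison just before the list, codes timepoint as categorical as a visit-specific contrast would need, and nowhere says main effects only. It also explores subgroups with the same model, although no antipsychotic-group term is listed, so the list cannot be complete for every use. An analysis plan that is not shown may supply the interaction.

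This softens the charge but does not remove it. The article fixes the terms down to the coding of timepoint, and an analyst who follows it fits the additive model. Reading the interaction in means adding a term that the authors did not list.

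Four stronger inferences are tempting and not supported:

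- **The trial loses power.** This depends on unstated inputs. With SD 3 at week 13, several scenarios stay above 80%. With equal effects at both visits, power rises.
- **The coefficient always leans to week 13.** Dropout is defined only by absence at week 26. If those patients leave before week 13, the weights are equal.
- **Nothing planned isolates week 26.** The ANCOVA does, though as a sensitivity analysis on patients with a week-26 weight. If it disagrees with the mixed model, the cause could be missing data or the averaging over visits.
- **The plan breaks a promise to study time trends.** The Discussion's phrase "thus allowing us to better ascertain drop-outs and temporal patterns in treatment response" contrasts 26 with 12 weeks of treatment and is not an analysis commitment.

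The equal variance implied by a random intercept is also secondary, because nothing in the article shows that the variances differ.

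**Conclusion.** The point holds as a mismatch between the stated primary comparison and the listed primary model. The single coefficient matches the week-26 effect only under a constant treatment effect, which the article neither states nor justifies.

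If the week-13 effect is half of a 2 kg week-26 effect, the target falls by 25% with complete data (1.50 kg) and by about 32 to 37% when 32 to 64 per arm have week 13 only (1.26 to 1.36 kg). Power then ranges from about 0.60 to 0.92, depending on the week-13 SD, the correlation and the timing of dropout. With no week-26 effect and a 1 kg week-13 effect, the test favours metformin in about 12 to 33% of trials. The week-13 effect and SD, the correlation and the week-13-only counts behind these sizes are assumptions. That the coefficient is an average over visits follows from the listed terms alone.

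**What to change.** Add treatment-by-timepoint to the fixed effects of the primary model, and name the model-based treatment contrast at week 26 as the primary estimate and test. Carry the same wording over to the secondary outcomes that use a similar model. Baseline weight-by-timepoint and an unstructured within-patient covariance are optional refinements.

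The change is about one sentence of model wording, best made before unblinding. The sample size stays at 128 completers and 256 recruited, and visits and data collection do not change. The price is a larger standard error than that of the pooled coefficient: with SD 4 at both visits and complete data, 0.707 against 0.612 to 0.680. That 0.707 is the precision on which the trial was sized.
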